### Statistical issues

#### Data analysis

Data will be analysed on an intention-to-treat basis. Analysis of data includes comparison of maternal baseline characteristics at randomisation, maternal morbidity and mortality until hospital discharge and 6 weeks post-partum, neonatal morbidity and mortality until hospital discharge, method of delivery, type of hospital care and days of maternal and neonatal hospital stay. Differences between groups with normally distributed data will be tested using the Student's *t *test and for data with a skewed distribution, a non-parametric Mann-Whitney U test will be used. Categorical data will be analysed with χ2 statistics. Calculation of the percentages will be based on the number of valid observations. Treatment effect will be presented as relative risk (RR) with 95% CIs, and where appropriate as absolute risk reduction with 95% CIs and number needed to treat. A p-value of less than 0.05 indicates statistically significance. To asses treatment effects between different categories of patients in the trial we will perform subgroup analysis: per gestational age of the fetus per week (34^+0 ^- 34^+6^, 35^+0 ^- 35^+6 ^and 36^+0 ^- 37^+0^), parity (women with versus women without a previous vaginal delivery), hypertensive related disease (gestational hypertension versus pre-eclampsia), the use of corticosteroids (administered prior to delivery versus no use), mode of delivery (vaginal delivery versus caesarean section), caesarean delivery in history (history of a caesarean delivery versus no history of caesarean delivery) and the Bishop score (< 2, 2-6 and > 6).

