### Procedures, recruitment, randomisation and collection of baseline data

Eligible women will be identified by the local research coordinator and/or the staff of participating hospitals. After counselling and reading the patient information form, patients will be asked for written consent. We will provide patient information in Dutch as well as several other languages (Turkish, French, Spanish and English), in order to facilitate inclusion of patients from cultural minorities. After informed consent, patient data will be entered in a web-based database, which will also facilitate randomisation.

Prior to randomisation, we will perform a digital examination to establish a Bishop score and we will measure cervical length. Women will be randomly allocated to either delivery within 24 hours (experimental arm) or expectant monitoring (control arm) until 37 weeks of gestational age. The study will be an open label study, as it is impossible to blind the health care workers and patients involved for the strategy to which the woman is allocated. Randomisation will be performed centrally with the use of a permuted-block design, stratified for recruiting centre. Randomisation will be 1:1 for intervention and expectant monitoring management. Although it will not be possible to prevent all cross-overs, both strategies will be performed according to strict criteria, as mentioned below.

At study entry baseline demographic, past obstetric and medical history will be recorded into the web-based Case Report Form (CRF) that is accessible through a closed part of a central website. Details of delivery, maternal and neonatal assessments during pregnancy or post-partum are recorded in the CRF. The collected data will be coded and processed with adequate precautions to ensure patient confidentially.

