A subset of 200 women will receive quality of life questionnaires prior to randomisation, one day after randomisation and subsequently after 1 week, 2 weeks, 6 weeks, 3 months and 6 months. Since the gestational age at delivery will differ between the two groups, we will ask the participating women also to complete questionnaires at 1 day and 2 days after delivery. A pain scale will be added to those questionnaires. We hypothesize differences on the emotional and anxiety scales prior to delivery and differences in physical scales after delivery (due to differences in instrumental delivery rates). The questionnaires will contain the Medical Outcome Study 36-Item Short Form Health Survey (SF-36), the European Quality of Life 6 dimensions 3 levels (EuroQoL 6D3L) with subsequent general health Visual Analogue Scale (VAS), the Hospital Anxiety and Depression scale (HADS), and the Symptom Check List (SCL-90), all validated in Dutch and English.

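### The stated tests use neither baseline quality of life nor the centre stratification; the useful gain is in quality of life, not in the primary composite

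*Protocol article*

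**What the plan says.** All references are to the protocol article.

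- **Data analysis, continuous outcomes.** Where the data are normal, the comparison is a two-sample t test ("Differences between groups with normally distributed data will be tested using the Student's"). Otherwise the choice is a rank test: "for data with a skewed distribution, a non-parametric Mann-Whitney U test will be used".
- **Data analysis, categorical outcomes.** The test is chi-squared: "Categorical data will be analysed with χ2 statistics". The effect measure is a plain ratio of risks: "Treatment effect will be presented as relative risk (RR) with 95% CIs". Where suitable, the absolute reduction and the number needed to treat are added. No covariate, stratification factor or baseline score is named for any outcome.
- **Procedures, recruitment, randomisation and collection of baseline data, allocation.** Balance is enforced within hospitals: "Randomisation will be performed centrally with the use of a permuted-block design, stratified for recruiting centre". The arms are meant to be of equal size: "Randomisation will be 1:1 for intervention and expectant monitoring management".
- **Same section, quality of life.** "A subset of 200 women will receive quality of life questionnaires prior to randomisation". Eight later questionnaires follow: six at 1 day, 1 week, 2 weeks, 6 weeks, 3 months and 6 months, and two at 1 and 2 days after delivery. The section expects differences on emotional and anxiety scales before delivery and on physical scales after it.
- **Secondary outcome measures.** Maternal quality of life is listed as a secondary maternal outcome.

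No other section plans a centre-stratified or baseline-adjusted analysis.

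**The concern.** The design creates two kinds of information that the stated tests do not use.

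The first is the quality-of-life score taken before randomisation. In a subset of only 200 women, a comparison that ignores it has a larger standard error than necessary and leaves chance differences at baseline uncorrected. This matters because the article states specific quality-of-life hypotheses.

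The second is centre. Blocks within centre balance the arms inside each hospital. If hospitals differ in outcome, a test that ignores centre carries a standard error slightly too large for the design used, so it errs on the conservative side. How much this matters depends on the outcome and has to be worked out separately for quality of life and for the rare binary endpoints.

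**Working it through.** **1. The plan's own figure.** Inputs from the Sample size section: 5% v 1%, two-sided alpha 5%, power 80%, 10% loss, target 680. With exact binomial power, a continuity-corrected chi-squared test needs 305 per arm: 610/0.9 = 678. Fisher's exact test needs 302 per arm: 604/0.9 = 672. Both agree with 680 to within 3%. The plain normal approximation gives 634 (285 per arm) and the Fleiss correction 740 (333 per arm). None of these takes credit for covariate or centre adjustment, so changing the analysis leaves 680 as it is.

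**2. Quality of life.** Inputs: 200 women, taken as 100 per arm under 1:1 allocation with complete return. The correlation rho between baseline and follow-up is not in the article; 0.3 to 0.7 is assumed.

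- Unadjusted detectable difference in SD units: (1.960 + 0.842) × sqrt(2/100) = 2.80 × 0.1414 = 0.396.
- Adjusting for baseline multiplies the variance by 1 − rho², so the detectable difference is 0.396 × sqrt(1 − rho²) and the equivalent unadjusted sample is 200/(1 − rho²).

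| rho | 1 − rho² | Detectable difference (SD) | Equivalent N | Power for 0.4 SD |
|---|---|---|---|---|
| unadjusted | 1 | 0.396 | 200 | 80.7% |
| 0.3 | 0.91 | 0.378 | 220 | 84.3% |
| 0.5 | 0.75 | 0.343 | 267 | 90.4% |
| 0.6 | 0.64 | 0.317 | 312 | 94.2% |
| 0.7 | 0.51 | 0.283 | 392 | 97.7% |

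**3. Primary composite and centre.** Expected events among 680 × 0.9 = 612 evaluable women: 306 × 0.05 + 306 × 0.01 = 15.3 + 3.1, about 18. Uncorrected chi-squared and centre-stratified Cochran-Mantel-Haenszel tests were compared by simulation, with 20,000 runs per scenario and 600 women in 10, 30 or 50 equal centres. The between-centre SD was 0, 0.5 or 1.0 on the logit scale. Number of centres and SD are assumptions.

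- Power at 5% v 1%: 83% to 87% with either test. Stratified minus unadjusted ranged from −0.6 to +0.2 percentage points.
- Type I error at 3% in both arms: the unadjusted test gave 4.5% to 4.7% at SD 1.0 (stratified 4.7% to 4.8%) and 4.8% to 5.4% at SD 0 to 0.5.
- Check: with no centre variation the simulated chi-squared power of 86.1% to 86.5% agrees with the exact 86.4% at 300 per arm.

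**4. A continuous outcome and centre.** If centre explains a share ICC of the variance, the adjusted standard error is sqrt(1 − ICC) of the unadjusted one. At an assumed ICC of 0.05 that is 0.975, so 2.5% smaller, and the unadjusted test has a true alpha of about 4.4%. At 0.01 the figures are 0.5% and 4.9%; at 0.10 they are 5.1% and 3.9%.

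**The case against.** **Quality of life is not in the list of analyses.** The Data analysis section does not name it, and a condensed article may leave its modelling to a fuller document. It is also true that the article nowhere says raw scores will be compared visit by visit; a reader might infer this, but a t test on change from baseline fits the sentence equally well. The point survives, because the t and Mann-Whitney rule is the only stated method that reaches quality of life, and the change-score reading does not rescue it. With equal SDs the change-score variance factor is 2(1 − rho). That is 1.40 at rho 0.3 (worse than ignoring baseline), 1.00 at 0.5 and 0.60 at 0.7, against 0.91, 0.75 and 0.51 for baseline adjustment.

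**The correlation is assumed.** This stands. At 0.3 the gain is modest, about 10% in equivalent sample. Baseline is taken during hypertensive disease in pregnancy and follow-up runs past delivery, so one constant correlation for all visits is unlikely.

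**Two visit clocks.** This also stands. Some questionnaires are timed from randomisation and some from delivery, and time to delivery differs by arm. One model over all visits would mix women before and after delivery unless the two sets are kept apart.

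**All tests discard precision.** A reader might infer this from the lack of adjustment throughout. It is not supported. The centre-stratified test gained nothing material on the primary composite in any scenario tried, and caesarean section, respiratory distress syndrome and the other neonatal outcomes have no pre-randomisation value to adjust for.

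**Conclusion.** The point holds in a limited form. The article fixes unadjusted tests although it collects baseline quality of life and stratifies by centre. For quality of life the cost is real: a detectable difference of 0.40 SD instead of 0.38 to 0.28 SD, resting on 100 women per arm, complete questionnaires and an assumed correlation of 0.3 to 0.7.

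For the primary composite the argument is consistency with the randomisation and avoidance of slight conservatism, not power. It would be wrong to conclude that the unadjusted tests are invalid, that the primary comparison is underpowered for this reason, or that 680 needs to change. The sizes for centre rest on assumed numbers of centres and between-centre variation, neither of which the article gives.

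**What to change.** **Quality of life.** Replace the t or Mann-Whitney comparison with a baseline-adjusted analysis reporting adjusted mean differences with 95% CIs. Use ANCOVA at named visits, or a mixed model with baseline score, time, arm-by-time and centre. Analyse the visits timed from randomisation and those at 1 and 2 days after delivery separately.

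**Binary outcomes.** Report a Mantel-Haenszel relative risk and risk difference stratified by centre. Pool small centres by a rule fixed before outcome data are seen and based on numbers recruited, not on events.

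**Sensitivity.** Keep the currently stated unadjusted analyses.

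**Cost.** Analysis-plan wording and some extra programming; no further patients or data. Centres without events add nothing to the stratified relative risk, which is why the pooling rule is needed with about 18 events expected. They still count in the stratified risk difference.

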#### Sample size

We hypothesize that immediate delivery can reduce maternal complications from 5% to 1%. Using a two sided test (alpha error 5%, beta error 20%) and assuming a 10% rate lost to follow-up and protocol violations, we aim to recruit 680 patients. This sample size is also large enough to assess whether there will be relevant differences in the primary neonatal outcome (incidence of RDS around 10% at 34 weeks versus 1-3% at 37 weeks).

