**Methods/Design:**

Pregnant women with severe gestational hypertension, mild pre-eclampsia or deteriorating chronic hypertension at a gestational age between 34^+0 ^and 36^+6 ^weeks will be asked to participate in a multi-centre randomised controlled trial. Women will be randomised to either induction of labour or expectant monitoring. In the expectant monitoring arm, women will be induced only when the maternal or fetal condition detoriates or at 37^+0 ^weeks of gestation. The primary outcome measure is a composite endpoint of maternal mortality, severe maternal complications (eclampsia, HELLP syndrome, pulmonary oedema and thromboembolic disease) and progression to severe pre-eclampsia. Secondary outcomes measures are respiratory distress syndrome (RDS), neonatal morbidity and mortality, caesarean section and vaginal instrumental delivery rates, maternal quality of life and costs. Analysis will be intention to treat. The power calculation is based on an expectant reduction of the maternal composite endpoint from 5% to 1% for an expected increase in neonatal RDS from 1% at 37 weeks to 10% at 34 weeks. This implies that 680 women have to be randomised.

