### Outcome measures

#### Primary outcome measure

The primary outcome measure will be a composite endpoint of maternal mortality, maternal complications (eclampsia, HELLP syndrome, pulmonary oedema, thromoembolic disease) and progression to severe pre-eclampsia. Eclampsia is defined as severe gestational hypertension or pre-eclampsia resulting in maternal seizures [14]. HELLP syndrome is defined as a complication of severe pre-eclampsia involving Hemolysis, Elevated Liver functions, and Low Platelets [14,15]. Thromboembolic disease is defined as deep-vein thrombosis, pulmonary embolism or both. Patients will be examined for deep-vein thrombosis by duplex Doppler if thrombosis is suspected from clinical examination. A diagnosis of pulmonary embolism will be confirmed by pulmonary angiography, computed tomography, magnetic resonance imaging or a ventilation-perfusion lung scan [16-18].

Progression to severe pre-eclampsia is defined as diastolic blood pressure equal/greater than 110 mmHg despite medication, systolic blood pressure equal/greater than 170 mmHg despite medication and/or proteinuria equal to/greater than 5 g/L.

The neonatal primary outcome will be respiratory distress syndrome (RDS). Diagnosis of RDS requires signs of respiratory distress, consistent radiologic features, and oxygen therapy with a fraction of inspired oxygen (FIO2) of 0.40 or greater for at least 24 hours or until death [19].

Secondary outcome measures

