## Discussion

Gestational hypertension (including chronic hypertension) and pre-eclampsia are important hypertensive disorders during pregnancy which are associated with increased maternal and neonatal morbidity and mortality. There is no consensus on how to manage these hypertensive disorders between 34 and 37 weeks 'gestation. Induction of labour will prevent maternal complications, but might also increase the neonatal morbidity due to the pre-term birth.

This trial will provide evidence as to whether or not induction of labour in women with a hypertensive disorder in the late pre-term period is an effective treatment to prevent severe maternal complication, without compromising the neonatal morbidity.

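### The statement that 680 women also suffice for RDS rests on infants born at 34 versus 37 weeks, which is not the contrast between the randomised arms

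*Protocol article*

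**What the plan says.** Under Statistical issues, Sample size, the 680 is derived for the maternal composite: 5% v 1%, two-sided 5% test, 80% power, and a 10% allowance for loss and protocol violations. The article then says of RDS: "This sample size is also large enough to assess whether there will be relevant differences in the primary neonatal outcome", and gives as its reason "incidence of RDS around 10% at 34 weeks versus 1-3% at 37 weeks". The abstract (Methods/Design) brings the same comparison into the power calculation, "for an expected increase in neonatal RDS from 1% at 37 weeks to 10% at 34 weeks", with 1% rather than 1-3% at 37 weeks.

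Four other sections determine what the arms will look like:
- Participant/Eligibility Criteria: entry at any time from 34+0 to 36+6.
- Interventions, immediate delivery: labour induced within 24 hours of randomisation.
- Interventions, expectant monitoring: delivery at spontaneous labour, on maternal or fetal deterioration, or by induction at 37+0.
- Data analysis: intention to treat, with subgroups by week of gestation.

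The status of RDS differs between sections. Outcome measures has "The neonatal primary outcome will be respiratory distress syndrome (RDS"), while the abstract has "Secondary outcomes measures are respiratory distress syndrome (RDS").

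**The concern.** The 10% v 1-3% difference would be seen between arms only if every woman were randomised at 34+0 and every expectant woman reached 37 weeks. The design does not produce that. The immediate arm delivers across 34, 35 and 36 weeks, so its RDS rate lies below 10%. Part of the expectant arm delivers before 37+0, so its rate lies above the 37-week figure. Both effects shrink the difference.

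The trial is meant to weigh maternal benefit against neonatal cost. A reader who accepts the adequacy sentence will expect a real increase in RDS to be detected, and may give a non-significant result more weight than it can carry.

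**Working it through.** **Evaluable number.** 680 × 0.9 = 612, or 306 per arm at 1:1 allocation.

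**The plan's own figure.** For 5% v 1%, Fisher's exact test reaches 80.1% power at 302 per arm. 604/0.9 = 672, within 3% of 680, and at 306 per arm exact power is 80.8%. The maternal calculation is reproduced.

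**Power formula for RDS** (pooled-variance two-proportion test, two-sided 5%, n per arm, p̄ the mean of p1 and p2):

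power = Φ{ [ |p1 − p2| − 1.96 √(2p̄(1 − p̄)/n) ] / √([p1(1 − p1) + p2(1 − p2)]/n) }

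**The quoted contrast, n = 306:** 10% v 1% gives 99.9%, 10% v 2% gives 98.7%, 10% v 3% gives 94.2%.

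**Arm-level contrast.** The article gives no entry mix, no RDS curve between 34 and 37 weeks and no share of expectant women reaching 37 weeks. What follows is assumed, apart from the two end rates.

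*Immediate arm.* RDS falls linearly from 10% at 34+0 to r at 37+0 (21 days). Entry is uniform over the 21 days and delivery is one day after entry, so mean delivery is on day 11:

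p1 = 10 − (10 − r) × 11/21, which is 5.3%, 5.8% and 6.3% for r = 1, 2 and 3%.

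*Expectant arm, all reaching 37 weeks.* p2 = r.

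*Expectant arm, half reaching 37 weeks.* The other half deliver evenly over the days from the day after entry to 37+0, on average day 16. Their rate is 10 − (10 − r) × 16/21 = 3.1%, 3.9% and 4.7%. Averaged with r, p2 = 2.1%, 3.0% and 3.8%.

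*One case in full.* For 6.33% v 3%: p̄ = 0.0467, so 1.96 √(2 × 0.0467 × 0.9533/306) = 0.0334. The difference is 0.0333 and the denominator is 0.0170. The argument of Φ is about −0.005, and power is 50%.

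**Power (%) at 306 per arm, for 37-week RDS of 1 / 2 / 3%.** Entry mixes are shares randomised in weeks 34/35/36.

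| Entry mix | RDS curve | All reach 37 weeks | Half reach 37 weeks |
|---|---|---|---|
| Uniform | linear | 86 / 68 / 50 | 56 / 41 / 29 |
| Uniform | log-linear | 60 / 48 / 36 | 40 / 30 / 23 |
| Later, 20/30/50 | linear | 74 / 53 / 36 | 44 / 30 / 21 |
| Later, 20/30/50 | log-linear | 41 / 32 / 24 | 27 / 21 / 16 |
| Earlier, 50/30/20 | linear | 93 / 80 / 63 | 67 / 51 / 37 |
| Earlier, 50/30/20 | log-linear | 76 / 63 / 50 | 53 / 42 / 31 |

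If three quarters reach 37 weeks, the only case at or above 80% is earlier entry, linear curve and r = 1% (83%). Over all 54 combinations, 50 fall below 80%.

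A coarser grid places entry at the start or middle of each week and varies the share of the remaining time gained from 25% to 100%. It gives 6% to 99%, with 130 of 144 combinations below 80%.

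**Detectable difference.** At 306 per arm, 80% power needs about 4.8% v 1% or 8.2% v 3%.

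**The case against.** On its own inputs the sentence is arithmetically right, and the article attaches 80% power only to the maternal endpoint. This stands: the fault is the choice of contrast, not a miscalculation.

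The lower figures depend on assumptions supplied here. This also stands. A reader might infer that RDS power is certainly far below 80%, and the document does not support that. With earlier-weighted entry, a linear curve and a 1% rate at 37 weeks, power is 93% if all expectant women reach 37 weeks and 83% if three quarters do.

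The 306 per arm may be pessimistic, since intention to treat keeps protocol violators in. At 340 per arm the linear, uniform-entry figures rise from 86/68/50% to 89/73/54% if all reach 37 weeks, and from 56/41/29% to 61/44/32% if half do. Eligible multiple pregnancies add infants, but their outcomes are correlated. Neither closes the gap.

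A reader might also infer that the trial plans to declare neonatal safety from a non-significant test, and so needs a non-inferiority margin. The text does not say that. The words "without compromising the neonatal morbidity" in the Discussion belong to a question the trial is to answer, not to a conclusion drawn from p > 0.05. Aims hypothesises increased neonatal morbidity, which a test for a difference fits. Data analysis promises 95% confidence intervals, so imprecision would be visible.

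**Conclusion.** The point holds as a should-fix. The adequacy statement for RDS is unsupported, because its only evidence is a contrast between gestational ages at birth that the randomised comparison will not reproduce. That much follows from the article alone. The size of the shortfall does not: across the tabulated assumptions power runs from about 16% to 93%, mostly below 80%, against 94% to over 99% on the quoted contrast. Where power reaches 80%, it takes a linear fall in RDS, a 1-2% rate at 37 weeks, and all or three quarters of expectant women reaching 37 weeks.

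The 680 for the maternal composite is not in question. The conflicting label for RDS is real but minor.

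**What to change.** Delete the adequacy sentence, or replace it with three items: the expected RDS rate in each randomised arm for the planned gestational-age mix and delivery timing; the assumptions behind those rates, including one 37-week figure or an explicit range used in both abstract and text; and the resulting power, or the detectable difference, at 306 per arm. Align the abstract's power statement with this. Call RDS the primary neonatal outcome in the abstract, as Outcome measures and Sample size already do.

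The cost is wording and a less favourable stated figure. No extra patients, no change of analysis and no non-inferiority margin are required.
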